### Intervention

The MINDxYOU online program is based on the principles of “third wave” psychotherapies, such as the promotion of wellbeing through the practice of mindfulness, compassion, acceptance, and spirituality [39]. The effectiveness of “third wave” interventions has been widely contrasted empirically, also in the case of health professionals [16], and the MINDxYOU program was designed based on the experience of the research group on previous projects, such as the Attachment-Based Compassion Therapy [40] and Smiling is Fun [41] online programs, and also considering the results of the HEROES [42] and the PSY-COVID projects, the latter being an international research project that evaluated the psychosocial impact of the COVID-19 pandemic on both the general population and specific populations (healthcare personnel, university students, etc.).

MINDxYOU is a self-guided online program particularly designed for healthcare workers in order to both monitor and support the individual’s mental health. This program will aid healthcare professionals to deal with their daily, work-related stress through the practice of mindfulness, compassion, and acceptance exercises, along with indications on how to apply these concepts to basic aspects of a healthy lifestyle (i.e., physical activity, sleep hygiene, balanced diet, and socialization).

The program is self-administered and will be delivered over the Internet and available via smartphone, tablet, and personal computer. During the first 8 weeks, there will be minimum support provided by an external professional unrelated to the research group, who will make weekly contact with participants via their preferred means (i.e., telephone, text message, email) to promote adherence to the intervention, encouraging the participant to keep on using the program and strengthening their commitment to the exercises. However, this contact will neither be used to add new educational content nor for assessment purposes, which will be entirely covered by the online platform with online links to the questionnaire(s) they need to complete; nor will it be used for counseling purposes.

The intervention begins with a welcome module that introduces the main aims and procedures of the platform. Participants are invited to share a written testimony of their main stressors in their workplace, and their feelings and personal needs. The external professional will read each testimony and respond to each one by offering a rationale for why the intervention can be beneficial for their case, enhancing motivation to complete the intervention. The testimonies will be analyzed and used to improve the contents of the intervention wherever possible.

After the welcome module, the program will be structured into 4 modules, each dedicated to a specific topic (see Table 1). Every module will contain animated videos with explanations of the aims and contents of the topic to be addressed, along with some examples of exercises that participants will then be able to practice on their own. Written material will also be provided to give participants a deeper understanding of the contents of the module, and audios with guided practices will be included for each exercise. PDF files and audios will be available for participants to download and save for use in the future or for practice outside of the web platform. Practice logs will also be available, and participants will be able to complete them on the online platform to enable the research team to check the completion of tasks. It is recommended that a period of 2 weeks be dedicated to each module, although participants will be free to adapt this to their needs. The first module, on mindfulness, will introduce most of the basic concepts of the intervention, and these will also be taken up in the following modules. The last module will focus on how to apply the concepts and practices of mindfulness and compassion concepts to key aspects related to a healthy lifestyle (i.e., physical activity, diet, sleep, and socialization). The estimated time required to complete the whole program is 8 weeks; after week 8, participants will no longer be contacted by the member of the research team. However, the program will continue to be available for use indefinitely.

### Assessment plan

All potential candidates will undergo an initial screening assessment conducted by a member of the research team who is a certified psychiatrist or clinical/health psychologist; this assessment will include MINI v7.0.2 to identify psychiatric disorders. Later, a baseline evaluation will be conducted, including an ad hoc sociodemographic questionnaire, primary and secondary outcomes, process variables, and cost-utility measures. After the baseline evaluation, the participants will be assessed again every 8 weeks. During the intervention, the participants will complete the SUS twice.

#### Diagnostic interview: Mini International Neuropsychiatric Interview (MINI) Version 7.0.2

MINI v7.0.2 [43] is a brief structured diagnostic interview for DSM-5 psychiatric disorders. It assesses the 17 most common disorders in mental health, those considered the most important to identify in clinical and research settings: major depressive episode, major depressive disorder, suicidal tendencies, suicidal behavior disorder, maniac episode, hypomanic episode, bipolar disorder type I, bipolar disorder with psychotic traits, bipolar disorder type II, other bipolar disorder, panic disorder, agoraphobia, social anxiety disorder, obsessive–compulsive disorder, post-traumatic stress disorder, alcohol abuse disorder, and substance abuse disorder. It takes approximately 15 min to administer, and the present study will use the Spanish version to verify that the participants do not present with any severe conditions. MINI has shown excellent psychometric properties, including high interrater reliability (*k* = 0.90 or higher) [43].

#### Primary outcome: Perceived Stress Scale (PSS)

PSS [37] consists of 10 items in which participants are asked to rate how unpredictable, uncontrollable, and overloaded they have found their life over the past month on a 5-point Likert-type scale (e.g., “how often have you felt that you were unable to control the important things in your life?”). Scores range between 0 and 40, and higher scores reflect higher levels of perceived stress. PSS was validated in Spanish [44], and this version presented good psychometric properties, including internal consistency (α = 0.81), test–retest reliability (*r* = 0.77), and sensitivity to change.

#### Secondary outcomes

The *Patient Health Questionnaire* (PHQ-9) [45] is a 9-item scale aimed at screening for depression in primary care and other medical settings. It assesses the frequency of depressive symptoms during the last 2 weeks using a scale between 0 (not at all) and 3 (nearly every day). The total score ranges between 0 and 27, with higher scores indicating higher severity of depression. PHQ-9 has presented excellent psychometric properties, including reliability, validity, and responsiveness [46].

The *Generalized Anxiety Disorder-*7 (GAD-7) [47] is a 7-item, self-report measure to assess the intensity of anxiety symptoms. It refers to the period of the past 2 weeks; each item is scored on a 4-point Likert-type scale, resulting in a total score that can range between 0 and 21, with higher values reflecting more severe anxiety symptoms. Good psychometric properties have been reported for GAD-7 in different populations, also for the Spanish version [48].

The *Brief Symptoms Inventory-18* (BSI-18) [49] is an adapted version of the original 53-item, self-report questionnaire [50] that is designed to offer rapid screening for the symptoms of psychological disorders. Each item is scored on a 5-point Likert-type scale, reflecting on the past 7 days. Scores on the 18 items are summarized on the Global Severity Index (GSI). The BSI-18 also includes three symptom scales: Somatization, Depression, and Anxiety, each comprising six items. The Spanish version [51] shows reliable and valid psychometric properties.

#### Process variables

The *Connor-Davidson Resilience Scale* (CD-RISC) [52] is a 10-item, self-report measure addressed at assessing resilience. Each item is scored on a 5-point Likert scale, and the total score, which ranges between 1 and 5, is calculated by averaging the scores of the items; higher scores indicate higher levels of resilience. The questionnaire has shown good psychometric properties in people with anxiety or stress-related disorders. The Spanish version [53] also presented good internal consistency (*α* = 0.86) and test–retest reliability (*r* = 0.87).

The *Five Facets of Mindfulness Questionnaire -15 item version* (FFMQ-15) [54] is an adaptation of the original 39-item FFMQ, a questionnaire measuring the five facets of mindfulness: *observing* (i.e., noticing internal and external experiences such as sensations, thoughts, or emotions), *describing* (i.e., labeling internal experiences with words), *acting with awareness* (i.e., focusing on one’s activities in the present moment as opposed to behaving automatically), *nonjudging of inner experience* (i.e., taking a non-evaluative stance toward thoughts and feelings), and *non-reacting to inner experience* (i.e., allowing thoughts and feelings to come and go, without getting caught up by them). Each subscale of FFMQ-15 includes 3 items, scored on a Likert-type scale (1–5). A score for each subscale, ranging between 5 and 15, can be computed by summing the items, where higher scores indicate higher levels of the mindfulness facet. FFMQ-15 presents good psychometric properties, similar to those of the original questionnaire, and the Spanish version also presented good internal consistency for every subscale [55].

The *Sussex-Oxford Compassion Scales* (SOCS) [56] consist of two self-report measures designed to evaluate self-compassion and other-compassion. Each measure consists of 20 items that are answered on a 5-point Likert-type scale. A total score of each scale can be calculated by summing the scores of the items; each total score ranges between 20 and 100, with higher scores indicating higher levels of compassion. The psychometric properties of the SOCS have proved to be good [56], and the Spanish adaptation is currently being validated by our research group.

The *Acceptance and Action Questionnaire-II* (AAQ-II) [57] is a common measure for assessing experiential avoidance, a key element of “third wave” psychotherapies that refers to the tendency to avoid thoughts, feelings, memories, sensations, and other internal experiences, and which is very commonly associated with worse mental health outcomes, as opposed to psychological flexibility. The scale presents 7 items scored on a 7-point Likert-type scale, and the total score is calculated by summing all the items. Higher scores mean higher experiential avoidance. AAQ-II shows good psychometric properties, including internal consistency (α = 0.84) and test–retest reliability (*r* = 0.79). The Spanish version has presented similar psychometric qualities [58].

#### Cost-utility variables

The five-level version of the *EuroQol five-dimensional classification system* (EQ-5D) [59] is a widely used health-related quality of life measure. First, participants are asked to report the severity (1 = no problems, 2 = mild, 3 = moderate, 4 = severe, 5 = extreme) of the problems they may present on the day of reporting with regard to each of the following five domains: mobility, self-care, usual activities, pain, and anxiety/depression. The combination of the answers given to these domains results in 3,125 different health states. The utility scores are obtained from the EQ-5D classification system and are used to rate patients’ health-related quality of life, which normally range between 0 (although it is possible to present negative scores) and 1 (i.e., “perfect health”). These utility values will be calculated using the Spanish tariffs of EQ-5D-5L [60]. EQ-5D utility values will be used to estimate quality-adjusted life-years (QALYs), a common measure to assess the outcomes associated with different treatments, both in terms of patients’ quality of life and survival [61]. EQ-5D also asks participants to use a visual analog scale (EQ-VAS) to record their current overall health status, ranging between 0 (worst imaginable health) and 100 (best imaginable health).

The *Client Service Receipt Inventory* (CSRI) [62] is one of the most widely used resource-use measurement tools; it describes and measures service utilization patterns as a basis for estimating associated costs across healthcare, social care, and community settings. In the present study, the Spanish version [63] will be used to collect retrospective data (last 2 months) on medication and service use. For medication intake, patients will be asked to bring their daily medication prescriptions, and the following information will be recorded: drug name, dosage, total number of prescription days, and daily dosage consumed. With regard to service use, patients will be asked about total visits to emergency departments, total days of general inpatient hospital admissions, number of diagnostic tests administered, and total visits to primary care physician, nurse, social worker, psychologist, psychiatrist, group psychotherapy, and other community healthcare professionals, specifying in each case if these services were provided by the public or by the private sector.

#### Implementation outcomes

In accordance with the Consolidated Framework for Implementation Research (CFIR) model, and taking into consideration the guidelines by Proctor et al. [64] and recommendations for implementation studies of online interventions by Hermes et al. [65], the present study will assess the following outcomes for the implementation process: acceptability, adoption, appropriateness, feasibility, fidelity, penetration, sustainability, and implementation costs, which will be measured along with the cost-utility variables. Treatment expectancies will be assessed before commencing the intervention, and participants will again be asked the same questions after completing the last module to assess their opinion [66]. In addition, focus groups will be held with the key players involved in the study in each province (i.e., Zaragoza and Malaga) once the intervention is complete (posttreatment) to qualitatively evaluate different domains related to the implementation.

The first of these, a*cceptability*, defined as the perception among implementation stakeholders that the intervention is useful or satisfactory, will be measured using the following measures:The *System Usability Scale* (SUS) [67], which is a 10-item questionnaire to measure the usability which is qualitatively related to the quality and acceptability of the intervention [68]. Usability is defined as the ease of use perceived by the users of the implemented technology. Use will be made of the Spanish version of SUS, which has presented good internal consistency (α = 0.81) [69].The *Attitudes towards Psychological Online Interventions* (APOI) [70], which includes 16 items to assess attitudes toward online interventions. APOI explores four dimensions; “Skepticism and Perception of Risks,” “Confidence in Effectiveness,” “Technologization Threat,” and “Anonymity Benefits”. APOI has shown good psychometric properties with acceptable to good internal consistency (α = 0.77) [70].The *Client Satisfaction Questionnaire adapted to Internet-based interventions* (CSQ-I) [71] is an 8-item, 4-point Likert scale questionnaire that assesses the general satisfaction of participants regarding the received intervention. The total score ranges between 8 and 32. The scale has shown excellent internal consistency (α = 0.93) [72].

Another construct that will be assessed in this regard is *appropriateness*, which is defined as perceived fit, relevance, or compatibility of the evidence-based practice for a given practice setting. We will use the *Intervention Appropriateness Measure* (IAM) [73], which includes 4 items designed to measure appropriateness of the intervention. The scale has shown good psychometric properties with high levels of internal consistency (α = 0.85 to 0.91) and test–retest reliability coefficients (*r* = 0.73 to 0.88).

The third domain that will be assessed in terms of implementation is *adoption*, defined as the intention, initial decision, or action to try or employ an evidence-based practice. In our study, adoption will be measured by the number of participants who agreed to use the program (considering the total number that were invited to use it) and actually accessed the online program. We will gather this information from the passive data collected by the online platform.

The *feasibility* of the intervention will also be studied. This is defined as the extent to which a new treatment can be successfully used or carried out within a given agency or setting. Feasibility will be measured with passive data gathered by the online platform regarding use of the program, specifically the frequency of use during the study. Use will also be made of the *Feasibility of Intervention Measure* (FIM) [73], which includes 4 items designed to measure the feasibility of the intervention. The scale has shown good psychometric properties with high levels of internal consistency (α = 0.85 to 0.91) and test–retest reliability coefficients (*r* = 0.73 to 0.88).

The fifth domain of implementation that will be analyzed is *fidelity*. In the context of online interventions, fidelity is defined as expected clinically meaningful use. This dimension will be measured with passive data collected by the online platform, specifically the number of modules and tasks completed. *Penetration*, in turn, will be measured considering the number of participants who agreed to use the intervention and completed at least 4 of the 5 modules of the program. Finally, *sustainability*, defined by the extent to which a new intervention is maintained, will be evaluated during the interviews and/or focus groups with the managers or directors of the different sites.

### Data analysis

#### Effectiveness analysis

Both intention-to-treat analysis and per-protocol analyses (i.e., those participants who complete at least 4 of the 5 modules of the intervention) will be performed. The analyses will include the description and elementary head-to-head comparisons between both phases (i.e., control vs. intervention). Specifically, the variables for each of the phases will be described by using descriptive statistics (means and 95% confidence intervals in the case of quantitative variables with normal distribution, medians, and interquartile range in the case of quantitative variables with non-normal distribution). To confirm the main hypothesis, all of the effectiveness variables (i.e., PSS and secondary outcomes) will be compared between the intervention and control phases. A multilevel regression analysis will be performed including the cluster as a random effect, and multivariate multilevel regression analysis will be performed to adjust for possible confounders. The magnitude of the effect of the improvement and the Number Needed to Treat (NNT) will also be reported, using the cut-off points already established in the primary outcome as criteria for considering whether a participant is a responder.

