### Study design

An effectiveness-implementation type 2 design will be used [33], since this study will assess both the effectiveness of the intervention and the implementation process in the same degree, as co-primary aims [34]. The empirical study will take a stepped wedge (SW) cluster randomized controlled trial design; this design implies that every participant starts the trial in the control phase (no exposure to the intervention), and then undertakes the intervention in a staggered and sequential way. Once it is completed (8 weeks), the maintenance phase takes place, during which the participant can continue to use the program at will, but without supervision. There will be three possible sequences (see Fig. 1), and each of the participating centers will be randomly assigned to one of them. The participants from each site will all follow the same sequence.

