**Fig. 1 Fig1:**
[figure not shown]
The three possible sequences of the study phases. *Note:* A = Control phase; B = Intervention phase; C = Maintenance phase. Each cell represents a period of 8 weeks

SW designs are particularly recommended when the intervention being tested has strong evidence of positive effects or is very unlikely to cause harm [35], which is the case of our study. The present work is considered a closed cohort study, since all the study participants will start at the same time and will be evaluated at different time-points to be defined beforehand; the inclusion of new participants will not be allowed once the trial has commenced.

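### The effectiveness model commits to no period term, so as written the control-versus-intervention contrast would absorb any common time trend in perceived stress

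*Protocol article*

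**What the plan says.** The Study design section of the Protocol article describes a stepped wedge in which "every participant starts the trial in the control phase (no exposure to the intervention), and then undertakes the intervention in a staggered and sequential way". Allocation is by centre: "There will be three possible sequences (see Fig. 1), and each of the participating centers will be randomly assigned to one of them". The note to Fig. 1 adds that "Each cell represents a period of 8 weeks", and the text after it describes a closed cohort in which "all the study participants will start at the same time and will be evaluated at different time-points". The Assessment plan sets the visits: "After the baseline evaluation, the participants will be assessed again every 8 weeks".

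The Effectiveness analysis section first announces "elementary head-to-head comparisons between both phases (i.e., control vs. intervention"), which it goes on to explain in terms of descriptive statistics by phase. It then says that the main hypothesis will be confirmed by comparing the PSS and the secondary outcomes between the intervention and control phases, and gives the model: "A multilevel regression analysis will be performed including the cluster as a random effect". The same sentence adds a multivariate multilevel regression for possible confounders and lists none.

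Neither model is labelled primary. No section mentions period, calendar time or a secular trend as a model term. No participant-level term is named, although each person is measured repeatedly.

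**The concern.** Randomising centres to sequences creates concurrent comparisons: at a given calendar time some centres are still in control while others have crossed over. Those comparisons are used properly only if the model adjusts for period. Without period, a phase contrast with a cluster random effect is close to a within-centre before-after difference, because exposed observations always come later.

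In this design, time is tied to exposure by construction. It is not a covariate to be left to a model for possible confounders.

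A trend is plausible. Recruitment starts in October 2022 in a workforce whose stress the Background describes as heightened by the pandemic, and the periods then run through different seasons. Repeated completion of the same questionnaires could also move scores. Falling stress would be credited to the programme, and rising stress would hide a benefit.

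The same phase difference feeds the secondary outcomes and, through the Economic evaluation section, the ICUR and ICER. It may also feed the NNT.

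**Working it through.** **Inputs from the protocol:** three sequences, 8-week periods, a common start and assessment every 8 weeks (Study design, Fig. 1 note, Assessment plan); six clusters, ICC 0.04, 24 analysed per cluster and d = 0.50 (Sample size). The plan gives no figure for time-trend bias, so there is none to reproduce. The 24 per cluster is taken as printed. The printed formula with its printed inputs gives 126 × 0.96 / (6 − 5.04) = 126, which is a separate matter; the bias multiplier hardly depends on cluster size.

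**Assumptions, because the document does not give them:** two clusters per sequence; crossovers after one, two and three periods; within-person correlation 0.5 to 0.7; linear trend b per 8 weeks; no true effect; total variance 1; normal approximation. Results come from exact generalised least squares.

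**Step 1: gap in calendar time.** Number the assessments 0, 1, 2, … in 8-week units. For each sequence, gap = mean time of exposed visits − mean time of control visits.

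| Assumed layout | Mean time, control | Mean time, exposed | Gap by sequence |
|---|---|---|---|
| A. First exposed visit at 1, 2, 3; maintenance excluded | (0+0+1+0+1+2)/6 = 0.67 | (1+2+3)/3 = 2.00 | 1.0, 1.5, 2.0 |
| B. First exposed visit at 2, 3, 4 (end of the intervention period); maintenance excluded | (3·0+3·1+2·2+1·3)/9 = 1.11 | (2+3+4)/3 = 3.00 | 1.5, 2.0, 2.5 |
| C. As A, four visits, maintenance counted as exposed | 0.67 | (1+2+3+2+3+3)/6 = 2.33 | 2.0, 2.0, 2.0 |
| D. As A, five visits, maintenance counted as exposed | 0.67 | (10+9+7)/9 = 2.89 | 2.5, 2.5, 2.5 |

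**Step 2: bias of the phase coefficient without period.** The model estimate is close to the average within-sequence gap times b.

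| Layout | Cluster effect only | Cluster and participant effects |
|---|---|---|
| A | 1.50 b | 1.54–1.55 b |
| B | 2.00 b | 2.02 b |
| C | 1.92 b | 1.97–1.98 b |
| D | 2.45 b | 2.48–2.49 b |

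The range is about 1.5 b to 2.5 b. More maintenance visits counted as exposed would push it higher. With period as a fixed effect the bias is 0 in every layout.

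**Step 3: size.** For a hypothetical b = 0.10 SD per 8 weeks, the shift is 1.5 × 0.10 = 0.15 to 2.5 × 0.10 = 0.25 SD. Relative to the planned effect, 0.15/0.50 = 30% and 0.25/0.50 = 50%.

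**Step 4: false positives at b = 0.10 SD.** They run from 0.20 to 0.98 with the cluster effect only, and from 0.55 to 1.00 with a participant effect added. The spread is wide because the cluster-only model ignores within-person correlation and misstates its standard error (layout A: model 0.102, actual 0.058–0.074). No single rate should be quoted.

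**Step 5: cost of adding period (cluster and participant effects fitted).** In layout B the standard error goes from 0.053–0.069 to 0.086–0.111 SD. Across all layouts it goes from 0.044–0.074 to 0.081–0.119 SD. Power for d = 0.50 stays at about 0.98 or more, with no cluster-by-period variance and no small-cluster correction allowed for.

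**The case against.** The best defence is that this is a condensed article and a fuller analysis plan may exist. The quoted sentence says what the model includes and does not claim to be a complete list; it names no fixed effects at all. Period could be among the unlisted confounders. That stands to this extent: a reader might infer that the plan rules out a period term, and the text does not say so. The omission is inferred from silence.

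What does not stand is treating period as detail that can wait. The article fixes a confirmatory contrast and a model structure, and anyone following them as written would get a biased estimate under any common trend. The confounder model does not cure this, because it promises no particular term.

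Three further readings are tempting but unsupported:

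- **The head-to-head comparison is an inferential test.** The section explains it through descriptive statistics and takes up hypothesis confirmation afterwards, so it can be read as already descriptive.
- **Regression to the mean adds to the apparent benefit.** The eligibility criteria set no minimum PSS score, so nothing selects people on a high baseline.
- **The bias always favours the programme.** A rising trend in stress would mask benefit.

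**Conclusion.** The point holds in this form: the stated analysis does not commit to a period term, and in this design the phase contrast is exposed to any common trend without one. The direction of the confounding follows from the design alone.

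The multiplier of about 1.5 to 2.5 per 8 weeks depends on the assumed Fig. 1 layout and on the handling of maintenance data. The trend of 0.10 SD is purely illustrative, since the document gives no trend and no within-person correlation. The finding does not show that a trend exists, or that the trial's false-positive rate takes any particular value. Because the validity of the primary estimate is at stake and the correction is nearly free, it should be settled before the data are analysed.

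**What to change.** State the primary model explicitly:

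- **Model:** PSS on phase (fixed) and categorical 8-week period (fixed), with random effects for cluster and participant. The participant effect is needed because the cohort is closed and measured repeatedly.
- **Maintenance data:** say whether maintenance-phase observations are excluded, counted as exposed or given their own phase level.
- **Small number of clusters:** with six clusters, name a small-sample correction.
- **Other outcomes:** use the same period adjustment for the secondary outcomes and for the phase differences behind the NNT, ICUR and ICER. The last three need their own wording, because they rest on responder status, costs and QALYs as well as on the PSS score.
- **Unadjusted comparisons:** say that any unadjusted phase comparison is descriptive only.

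For the PSS this takes a few sentences, with no change to recruitment or visits. The price is the larger standard error shown above, which is the precision that the design actually offers.
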